**Outcomes**

Outcomes have been chosen as events that are well recorded by GPs as part of routine patient care, regardless of where a diagnosis is made (by the GP or in secondary/tertiary centres). Numerous studies have been published looking at these outcomes using data from the GPRD/QRESEARCH and validity has been shown to be high (GPRD, 2010; QRESEARCH, 2010). The following outcomes will therefore be ascertained for all patients in the cohort:

- Death
- Change in Weight
- Change in BMI
- Diabetes
  - First diagnosis
  - Progression to monotherapy with oral antidiabetic agent
  - Progression to polytherapy with oral antidiabetic agents
  - Progression to insulin therapy
  - Resolution (noted in GP record as patient removal from diabetes QOF register)
- Cardiovascular disease
  - Incident MI
  - Incident stroke
  - Onset of hypertension
  - Onset of angina
  - Improvement of hypertension determined by permanently stopping antihypertensive medication, i.e. at least 6 months without a further prescription
- Osteoporotic Fractures (hip, spine, wrist)
- Acute liver injury as indicated by a diagnostic code or a record of alanine transferase at >3X upper limit of normal in patients without chronic liver disease.
- Fatty liver
- Incident cancer diagnoses
- Obstructive sleep apnoea
- Change in lipid profile

In addition, within the GPRD, Hospital Episode Statistics (HES) data will be available for a large proportion of the cohort. We will therefore be able ascertain post-operative outcomes, including post-operative haemorrhage, post-operative infection, ITU admission, re-admission to hospital and re-operation. Also, within the GPRD, detailed information on acute coronary events will be available via linkages with the Myocardial Ischaemia National Audit Project (MINAP).

The research team has considerable experience in developing algorithms for determining outcomes based on both GPRD and is developing expertise with HES data – algorithms for specific outcomes are available on request.

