8. We intend to divide the study into two separate research papers; one addressing changes in weight and BMI, and the other addressing all other outcomes.
9. **ADDITIONAL AMENDMENT 22 MAY 2014:** We plan to compare the risk of cardiovascular events in patients prescribed sibutramine with those prescribed orlistat. Sibutramine marketing was suspended in 2010 due to an increased risk of adverse cardiovascular outcomes. A review by the European Medicines Agency, found an “increased risk of non­fatal myocardial infarction and stroke, which outweighed the possible benefits of the medication through weight­loss” (Williams, 2010)[2]. This risk was clarified by the Sibutramine Cardiovascular Outcomes Trial (SCOUT; James et al, 2010), which examined cardiovascular outcomes in those at increased risk of cardiovascular events (i.e. individuals with diabetes mellitus, pre­existing cardiovascular disease or both). SCOUT randomized over 10,000 patients to either sibutramine or placebo. The primary outcome was time from randomization to non­fatal myocardial infarction, non­fatal stroke, resuscitation after cardiac arrest, and cardiovascular death. The risk of a primary outcome event was increased by 16% in the sibutramine group compared with placebo (hazard ratio, 1.16; 95% confidence interval [CI], 1.03 to 1.31; P=0.02), with overall incidences of 11.4% and 10.0%, in the two groups, respectively. This increase in primary outcome events was made up of non­fatal cardiovascular events, rather than cardiovascular death (hazard ratio, 0.99; 95% CI, 0.82 to 1.19; P=0.90). Also the increased risk was only shown in the groups with pre­existing cardiovascular disease (who previously had been excluded in prescribing guidance).

Orlistat remains the only prescribed drug for weight loss in the EU, and to date, no direct comparison has been made between orlistat and sibutramine regarding the risk of vascular outcomes. We will directly compare the risk of myocardial infarction and all cause mortality in patients prescribed orlistat and sibutramine. These outcomes are already included in this study, but the direct comparison between orlistat and sibutramine was not previously specified. This work will be done as part of an Epidemiology MSc summer project, by [name]. Specifically we will:

- 1. determine the relative risk of myocardial infarction (both fatal and non­fatal) in patients prescribed sibutramine or orlistat

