  2. determine the relative risk of myocardial infarction in high­risk patients (i.e with cardiovascular risk factors) prescribed sibutramine or orlistat
  3. determine time to all­cause mortality in patients prescribed sibutramine or orlistat

1. Analysis plan

Initially, basic descriptive analyses of event rates will be conducted in each treatment group. Cox proportional hazard models will be used to investigate univariable and multivariable hazard ratios for the outcomes. Adjustment will be made for potential confounders (covariates to be assessed will include age, sex, weight, BMI, smoking status, alcohol consumption and a range of co-morbidities such as coronary heart disease, hypertension and diabetes). Following traditional regression analysis, propensity scores will be calculated to further explore possible prescribing biases and confounding, based on patient status with respect to the covariates listed above, and their orlistat/sibutramine exposure status. Our primary intention is to match sibutramine and orlistat patients with similar propensity scores, excluding any patients with scores in non-overlapping regions of the score distribution. Cox proportional hazards models will then be used to calculate Hazard Ratios for each outcome. Sensitivity analyses will also be used to estimate how large an effect an unknown confounder would need to have to eliminate or bring about any observed effect. We will also determine whether any effect is modified by age, sex, and area level social deprivation.

The cohort of obese patients already extracted contains over 27,000 patients prescribed sibutramine and 90,000 patients prescribed orlistat. Assuming a baseline 7% annual event rate (a two sided type I error rate of 0.05, and power set at 90%) to detect a 10% difference in hazard ratio between orlistat and sibutramine would require a sample size of 19,000 patients prescribed sibutramine and 58,000 patients prescribed orlistat. Assuming orlistat is not associated with an increased risk of vascular events, we estimate we have adequate power to detect an increased risk of MI, similar to the increased risk of MI and stroke detected in the SCOUT trial.

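### The sibutramine v orlistat comparison is motivated by excess MI and stroke, but its head-to-head endpoints are MI and all-cause mortality, and its power sentence assigns a composite effect to MI alone

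*Protocol*

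**What the plan says.** All of this is in the protocol. Item 9 of the Amendment opens with a broad aim: "We plan to compare the risk of cardiovascular events in patients prescribed sibutramine with those prescribed orlistat". It supports the aim with a European regulatory review that found a raised risk of non-fatal MI "and stroke, which outweighed the possible benefits of the medication through" weight loss. It then cites a placebo-controlled sibutramine trial whose primary outcome combined non-fatal MI, non-fatal stroke, resuscitated cardiac arrest and cardiovascular death. The composite HR was 1.16 (95% CI 1.03 to 1.31; 11.4% v 10.0%). Item 9 attributes the excess to non-fatal events, with cardiovascular death at HR 0.99 (0.82 to 1.19). The gap to be filled is that "no direct comparison has been made between orlistat and sibutramine regarding the risk of vascular outcomes".

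The endpoints follow: "We will directly compare the risk of myocardial infarction and all cause mortality in patients prescribed orlistat and sibutramine". The three numbered aims match that sentence:

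- the first is to "determine the relative risk of myocardial infarction (both fatal and" non-fatal);
- the second is to "determine the relative risk of myocardial infarction in" high-risk patients;
- the third is time to all-cause mortality.

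The analysis plan under item 9 claims adequate power for an increased risk of MI "similar to the increased risk of MI and stroke detected in the SCOUT trial". The Outcomes section lists "Incident stroke" among the outcomes to be ascertained for all patients in the cohort.

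**The concern.** The aim, the safety signal, the stated evidence gap and the power benchmark all include stroke or vascular events generally. The endpoints do not, and the protocol does not say why. If sibutramine's excess lies partly or mainly in stroke, the comparison can find no difference in MI or death without having examined the event that carries the risk. Under an aim worded as cardiovascular events, such a result is open to being read more widely than the data allow.

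The power claim has a related fault. An effect observed on a four-part composite is assumed for one of its parts, and the protocol offers no component figure to justify that.

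**Working it through.** **1. Where stroke appears in item 9**

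| Element | Events covered | Stroke included? |
|---|---|---|
| Opening aim | cardiovascular events | yes, by its breadth |
| Regulatory signal | non-fatal MI and stroke | yes |
| Cited trial's primary outcome | non-fatal MI, non-fatal stroke, resuscitated arrest, cardiovascular death | yes |
| Evidence gap | vascular outcomes | yes, by its breadth |
| Three numbered aims | MI; MI in high-risk patients; all-cause mortality | no |
| Power benchmark | MI and stroke | yes |

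Item 9 notes, in support of MI and mortality, that both are already study outcomes. The same is true of stroke. Data quality does not explain the omission either: the Outcomes section describes its listed events as well recorded in general practice and of high validity.

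**2. What mortality can recover.** A non-fatal stroke never counts as an event in an all-cause mortality analysis. A fatal one counts, but is pooled with deaths from every other cause. Item 9 places the excess in non-fatal events, so this endpoint is a poor substitute.

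**3. The plan's sample size.** Inputs from item 9: 7% annual rate, 10% relative difference, two-sided 0.05, 90% power, allocation 19,000:58,000, so k = 58/19 = 3.053. Taking 7.7% v 7.0%:

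n(sibutramine) = [1.960·√((1+1/k)·p̄(1−p̄)) + 1.282·√(p₁(1−p₁) + p₂(1−p₂)/k)]² / (p₁−p₂)²

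With p₁ = 0.077, p₂ = 0.070 and p̄ = 0.0717, this gives 19,293 sibutramine and 58,894 orlistat patients. The stated 19,000 and 58,000 are reproduced to within 2%, so there is no arithmetic error. However, the 7% rate is not tied to any endpoint.

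**4. What the power sentence needs for MI alone.** For the available 27,000:90,000 patients, the sibutramine share is p = 27/117 = 0.231, and the events required at 90% power are D = (1.960+1.282)² / [p(1−p)(ln HR)²].

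- HR 1.16: 10.51 / (0.1775 × 0.1484²) = 2,688 events.
- HR 1.10: 10.51 / (0.1775 × 0.0953²) = 6,517 events.

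Whether MI alone yields 2,688 events depends on an MI rate that the protocol does not give. For illustration, take an assumed MI rate λ, three years of follow-up (also assumed) and a true MI HR of 1.16. Expected events are 27,000(1−e^(−1.16·3λ)) + 90,000(1−e^(−3λ)):

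| Assumed λ per year | Events | Power |
|---|---|---|
| 0.2% | 726 | 39% |
| 0.5% | 1,806 | 76% |
| 1.0% | 3,583 | 96% |

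Even these figures take 1.16 as the MI effect, which is the unsupported step. A composite hazard ratio does not determine its components, and item 9 reports only one of them, cardiovascular death.

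**5. Precision of an MI-or-stroke endpoint.** If r is the ratio of strokes to MIs, the SE of the log HR relative to MI alone is at best 1/√(1+r). For an assumed r of 0.5 this is 0.82, and for r = 1.0 it is 0.71. The protocol gives no value for r.

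**The case against.** The strongest reply is that the scope is declared. Item 9 moves from a general opening to an explicit endpoint sentence and three aims that agree with it, describes the work as a student summer project, and never promises to cover every vascular event. MI is a cardiovascular event, so this is a narrow choice and not a factual error. It is also fair that nothing in the protocol commits the authors to a conclusion wider than MI and death. Both points stand as description. They do not explain why one of the two events in the motivating signal is left out, nor do they support the power sentence.

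Other parts of the reply succeed against stronger readings that a reader might infer:

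- **That half of the signal is lost.** Stroke is one of two named event types, but the protocol never splits the trial's excess between them.
- **That stroke is never examined for sibutramine.** Study Design provides for a secondary analysis of sibutramine exposure, and stroke is a cohort outcome. What is missing is the head-to-head contrast with orlistat.
- **That the mortality endpoint is pointless.** The HR of 0.99 is for cardiovascular death, against placebo, in patients at raised cardiovascular risk. It does not show that all-cause mortality against orlistat is uninformative.
- **That adding stroke reproduces the cited trial's result.** That composite also contains resuscitated arrest and cardiovascular death, and its comparator was placebo.

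The reply is also right that the Outcomes section names stroke without defining it (algorithms are available on request), and that item 9 says the cohort has been extracted, not that strokes have been coded.

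**Conclusion.** The point holds as an unexplained mismatch. Item 9's aim, rationale and benchmark include stroke; its head-to-head endpoints do not, and mortality does not fill the gap. The power sentence transfers a composite effect to MI without support. The planned sample size itself reproduces and is not in question.

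The size can be stated only by event type: one of the two in the signal has no direct comparison. The share of excess risk missed cannot be estimated from the document. A reader might also infer a precision gain of 18 to 29% from the ratios in step 5 of the working. That range rests wholly on an assumed stroke-to-MI ratio, ignores that a patient with both events counts once, and concerns a different estimand: if the MI and stroke effects differ, a composite could dilute either. The case for stroke therefore rests on answering the stated question, not on precision. The change should be made before the comparison is analysed; the flaw does not invalidate the MI or mortality results for what they are.

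**What to change.** In item 9 of the Amendment:

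1. Add incident stroke, and time to first MI or stroke, as outcomes of the sibutramine v orlistat comparison. Cite the study's algorithm for stroke and use the same Cox and propensity-matched models.
2. State that conclusions drawn from MI alone apply to MI only.
3. Reword the power sentence so that HR 1.16 is described as the effect on the cited trial's composite, and name the endpoint to which the 7% annual rate belongs.
4. Where MI-or-stroke is set beside that trial, say that the composite differs and that the comparator was placebo.

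If stroke cannot be added, narrow the opening aim and the power reference to the endpoints kept, and give the reason.

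The cost is one or two further models, a short amendment, slight multiplicity, and the coding of strokes in the extracted cohort if that has not been done. No new patients are needed.

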**Exposures**

Exposures will be defined as follows:

- First record of bariatric surgery with at least 12 months prior UTS registration
- A first prescription for orlistat with at least 12 months prior registration to ensure incident usage
- A first prescription for sibutramine with at least 12 months prior registration to ensure incident usage

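### The sibutramine-orlistat comparison names neither calendar year nor prior use of the other drug, although the two drugs have different start windows and first use is defined separately for each

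*Protocol*

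**What the plan says.** Item 9 of the Protocol's Amendment section (22 May 2014) adds a head-to-head comparison of sibutramine and orlistat for MI and all-cause mortality.

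- **Adjustment.** For the Cox models, "covariates to be assessed will include age, sex, weight, BMI, smoking status, alcohol consumption". The same sentence adds co-morbidities, with coronary disease, hypertension and diabetes as its examples.
- **Propensity score.** It is to be "based on patient status with respect to the covariates listed above, and their orlistat/sibutramine exposure status". Nothing is added to the list.
- **Use of the score.** "Our primary intention is to match sibutramine and orlistat patients with similar propensity scores", with patients in non-overlapping parts of the score distribution excluded. No match on index date or year is mentioned.
- **Availability.** "Sibutramine marketing was suspended in 2010 due to an increased risk of adverse cardiovascular outcomes", whereas "Orlistat remains the only prescribed drug for weight loss in the EU".
- **Who is exposed.** The Exposures section defines "A first prescription for orlistat with at least 12 months prior registration to ensure incident usage" and, separately, "A first prescription for sibutramine with at least 12 months prior registration to ensure incident usage". Neither definition requires that the other drug has not been used before.
- **Switching.** The crossover rules in Statistical Analysis and Covariates, and in Amendment item 7, concern orlistat and surgery only. Amendment item 5 follows orlistat patients to the end of follow-up whatever treatment comes later.

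**The concern.** Two features of the comparison are left open.

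**Calendar time.** The groups differ by construction in when treatment could start: sibutramine up to 2010, orlistat up to at least 2014. A post-suspension orlistat starter had zero probability of receiving sibutramine. The propensity score, fitted without year, still gives that patient an ordinary positive value and makes the patient available as a match. Trimming on the score cannot help, because the score lacks the variable that separates the groups. The treated-versus-untreated cohorts do not share this gap, since their controls are tied to the treated patient's index date (Study Design and Study Population). The head-to-head comparison has no such link.

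**Prior use of the other drug.** A patient who took both drugs meets both exposure definitions and could qualify for either group. Those who come to a drug second may have stopped the first because it failed or was not tolerated. That history may be related to risk, and it is not among the covariates.

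At stake is a small effect. The comparison is sized for a 10% difference and refers to a hazard ratio of 1.16 from the cited randomised trial. A modest time-related bias could create or hide an effect of that order.

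**Working it through.** **1. The plan's own sample size.** Item 9 states 19,000 sibutramine and 58,000 orlistat patients for a 7% annual event rate, a 10% difference, two-sided 0.05 and 90% power. Two proportions, 7.7% versus 7.0%, with r = 3 orlistat patients per sibutramine patient:

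n = [1.960·√(p̄q̄(1+1/r)) + 1.2816·√(p₁q₁ + p₂q₂/r)]² / (p₁−p₂)²

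Here p̄ = (0.077 + 3×0.070)/4 = 0.07175. The two terms are 0.5841 and 0.3903, so n = 0.9744²/0.007² ≈ 19,377, with 58,131 on orlistat. The stated figures reproduce within 2.0% and 0.2%. The point does not rest on an arithmetic error.

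**2. What the adjustment can reach.**

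| Element of the plan | Contains index year? | Contains prior use of the other drug? |
|---|---|---|
| Cox covariates (item 9) | not named | not named |
| Propensity score (same list) | not named | not named |
| Matching and trimming | on the score only | on the score only |
| Exposure definitions | no shared period set | each drug taken alone |
| Crossover rules | – | orlistat and surgery only |

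**3. Possible size of the calendar-time bias.** The documents give no secular trend and no distribution of start dates, so both inputs are assumptions. Suppose the outcome rate falls by a fraction d per calendar year, sibutramine starts are on average g years earlier, and the drugs do not differ. The spurious hazard ratio for sibutramine is then approximately (1−d)^(−g).

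For the low end of g, the documents offer one rough clue. Sample Size/Power Calculation gives about 80,000 orlistat patients, in a protocol text that already mentions the suspension. Item 9 gives 90,000. If the counts are comparable, which is uncertain because one is a database count and the other an extracted cohort, about 10,000/90,000 = 11% are later additions. If those started on average 6 years after the rest (assumed), they shift the mean by 0.111 × 6 = 0.67 years. The gaps of 2 and 4 years are further assumptions and would also need start dates to differ before 2010.

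| Assumed annual decline | g = 0.67 | g = 2 | g = 4 |
|---|---|---|---|
| 2% | 1.014 | 1.041 | 1.084 |
| 3% | 1.021 | 1.063 | 1.130 |
| 5% | 1.035 | 1.108 | 1.228 |

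If recorded rates rose instead, the bias would run the other way. No figure can be put on the prior-use part, because the number of dual users is not given.

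**4. Room for a restriction.** Against its own requirement, the plan has slack of 1 − 58,000/90,000 = 35.6% of orlistat patients and 1 − 19,000/27,000 = 29.6% of sibutramine patients.

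As a second check, take Schoenfeld power for HR 1.10 at the plan's 7% rate with 27,000 sibutramine patients. With a the sibutramine fraction and D the events:

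Power = Φ(ln 1.10·√(D·a(1−a)) − 1.960), D = 27,000×(1−0.93^1.1) + 0.07×(orlistat n)

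| Assumed loss of orlistat patients | Power |
|---|---|
| none | 95.7% |
| 20% | 94.7% |
| 40% | 93.0% |
| 50% | 91.5% |
| 60% | 89.2% |

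These figures hold sibutramine at 27,000, ignore losses in matching and depend on the 7% event rate, which is not examined here.

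**The case against.** The best defence is that the list is illustrative. It is introduced as what the covariates will include, and a separate analysis plan might add year or settle how dual users are handled. A reader might infer that year is excluded from the models; the text supports only that it is not named. Even so, item 9 sets out its own analysis plan and ties the score to the listed covariates, so the plan followed as written has no year in the score.

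Three further readings go beyond the documents.

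- **That the bias is as large as the target effect.** This needs a steep trend and a gap of several years, both assumed. The rough clue from the two orlistat counts gives about 1.01 to 1.04.
- **That switchers are counted in both arms.** The text is silent. It lets a patient qualify for either group, but nowhere says that one person enters both.
- **That all 27,000 and 90,000 patients are analysed, or that any secular change is charged to sibutramine.** Those are the numbers in the extract, and matching and trimming will reduce them. Adjustment for smoking, hypertension, diabetes and coronary disease would absorb part of a trend.

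There are also partial safeguards. The sensitivity analysis in Limitations, which censors orlistat at early 2009, would drop every post-suspension starter. It was written for over-the-counter use in the orlistat analysis, not for this comparison, and it does not balance earlier start dates. The unknown-confounder analysis is generic, whereas index year is known and measured. Neither addresses dual users.

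Finally, the comparison is a secondary addition, and the surgery objective is untouched.

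**Conclusion.** The point holds as a gap in the design of the item 9 comparison. By the Protocol's own account the two drugs have different start windows. Neither index year nor prior use of the other drug is named for the models or the score, and no rule assigns patients who used both. Orlistat starters after the suspension are admitted without any possible sibutramine counterpart, and trimming on the score cannot detect them.

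Secular change in MI or death rates may therefore be confounded with drug. The documents establish neither direction nor size. The range of about 1.01 to 1.23 rests wholly on assumed declines of 2-5% per year and assumed mean gaps of about 0.7 to 4 years. Its upper part exceeds the 10% difference sought and its lower part is negligible. That uncertainty, together with how easily the gap can be closed, is the reason to act before the comparison is run.

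A reader might also infer that follow-up must end at the suspension because later sibutramine time is unexposed. The documents do not support that. Amendment item 5 deliberately takes an intention-to-treat-type approach for orlistat, and the choice between the two is one of estimand.

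**What to change.** Amend item 9 to:

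1. restrict both groups to first prescriptions before the 2010 suspension, and state the exact date used;
2. add index year to the Cox models and the propensity score, or match within year, since start dates may also differ before 2010;
3. define each patient's index drug as the first of the two, with no earlier prescription for the other, so that each patient belongs to one group;
4. state how later switching between the two drugs is handled in the main and sensitivity analyses.

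Ending follow-up at the suspension date is at most an optional sensitivity analysis.

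The cost is the loss of post-suspension orlistat starters, who have no sibutramine counterpart, and of second-line users of either drug. Index date is already needed to define exposure, so no new data are required. The remaining numbers should be counted before the analysis and set against the plan's own requirement of 58,000 orlistat and 19,000 sibutramine patients (90,000 and 27,000 available). The loss of second-line sibutramine users needs particular attention, as the slack there is 8,000 patients.

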**Sample Size/Power Calculation**

Counts received from the GPRD show:

- ~2,000 registered patients have had bariatric surgery, with a mean follow up of 2.4 years
- ~80,000 patients have received a prescription for orlistat
- >1.4 million patients have a BMI >=30

QRESEARCH contains data on a similar number of patients to GPRD and we therefore anticipate the number of eligible patients for this study would be roughly double the numbers shown above.

Assuming we match 5 untreated patients to each patient with an obesity intervention, we would have 80% power to detect a reduction in mortality over 4 years amongst those undergoing surgery from 5% to 3.9% (over the whole 4 year period).

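### The claim of adequate power for MI in the sibutramine-orlistat comparison rests on an unsourced 7% annual rate far above the protocol's other figures, so power for MI is undetermined

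*Protocol*

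**What the plan says.** Protocol, Amendment, item 9 (22 May 2014) adds a direct comparison of sibutramine with orlistat. It has three aims: MI, MI in high-risk patients, and all-cause mortality. The analysis plan under that item sizes the comparison as follows.

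- Rate: "Assuming a baseline 7% annual event rate". The event is not named and no source is given.
- Error rates: "a two sided type I error rate of 0.05, and power set at 90" per cent.
- Effect: "to detect a 10% difference in hazard ratio between orlistat and sibutramine".
- Result: the comparison "would require a sample size of 19,000 patients prescribed sibutramine and 58,000 patients prescribed orlistat".
- Available: the extracted cohort "contains over 27,000 patients prescribed sibutramine and 90,000 patients prescribed orlistat".
- Conclusion: "we estimate we have adequate power to detect an increased risk of MI", of a size similar to the excess in the cited trial. Item 9 gives that excess as a hazard ratio of 1.16.

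Two other places give event frequencies. Item 9 reports the cited trial's four-component composite "with overall incidences of 11.4% and 10.0%, in the two groups, respectively" (sibutramine first, then placebo), in patients at raised cardiovascular risk, without the length of follow-up. Sample Size/Power Calculation states, for the surgery comparison, that "we would have 80% power to detect a reduction in mortality over 4 years amongst those undergoing surgery from 5% to 3.9" per cent.

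The analysis plan also says that the main intention is to match on the propensity score and drop patients in non-overlapping regions. It fixes no matching ratio.

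**The concern.** The calculation works as if 7% of patients had the event within one year. The outcomes of the comparison are MI and all-cause death in obese patients prescribed a weight-loss drug in primary care. An annual rate of 7% is about 25% over 4 years, against the 5% mortality over 4 years that the same protocol assumes for obese patients without surgery. It would also be high beside a broad cardiovascular composite in a trial population chosen for high risk, and MI is only part of that composite.

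The rate carries the whole conclusion. This is a drug-safety comparison, and a null MI result would be read alongside a written statement that power was adequate. If events are much rarer than assumed, that statement could lend the null result more weight than it deserves. The high-risk subset (aim 2) has no calculation of its own.

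**Working it through.** **1. Reproduce the stated sample size.** Two-proportion formula, no continuity correction, one year at risk, k = 58/19 = 3.05 orlistat patients per sibutramine patient:

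n(sibutramine) = [1.960·√((1 + 1/k)·p̄(1 − p̄)) + 1.282·√(p1(1 − p1) + p2(1 − p2)/k)]² / (p1 − p2)², where p̄ is the weighted mean risk.

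- 7.7% v 7.0%: about 19,290 sibutramine and 58,890 orlistat patients.
- Hazard ratio 0.90, that is 1 − 0.93^0.9 = 6.32% v 7.0%: about 18,990 and 57,980.

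Both agree with 19,000 and 58,000. The arithmetic is sound and only the rate is in question.

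**2. Set 7% per year against the protocol's other figures.**

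- Mortality of 5% over 4 years: −ln(0.95)/4 = 1.28% per year. 7/1.28 = 5.5. Conversely, 1 − 0.93⁴ = 25% over 4 years.
- Composite of 10.0% on placebo: ln(0.90)/ln(0.93) = 1.45, or −ln(0.90)/0.07 = 1.51. It equals 7% per year only if follow-up was about 1.5 years. The protocol does not give the duration; assumed durations of 2, 3, 4 and 5 years give 5.3%, 3.5%, 2.6% and 2.1% per year.

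**3. Events needed for the effect in the disputed sentence, hazard ratio 1.16.** Schoenfeld: D = (1.960 + 1.282)² / [p(1 − p)·(ln 1.16)²], with p the sibutramine share; the numerator is 10.51 and (ln 1.16)² = 0.02203.

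- 27,000 and 90,000 (p = 0.231, p(1 − p) = 0.1775): D ≈ 2,690, which is 2.3% of 117,000.
- 1:1 matching, at most about 27,000 pairs (p(1 − p) = 0.25): D ≈ 1,910, which is 3.5% of 54,000.

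**4. Power over an assumed range.** The protocol gives neither an MI rate nor a follow-up length for these drug cohorts. Assume an MI rate of 0.2-0.5% per year on orlistat and 3-5 years of follow-up, so a cumulative risk of 1 − exp(−0.006) = 0.60% to 1 − exp(−0.025) = 2.47%. Expected events are (1.16·n1 + n2) × risk, and power = Φ(√(D·p(1 − p))·ln 1.16 − 1.96).

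| Analysis set | 1.16·n1 + n2 | Events | Power, HR 1.16 |
|---|---|---|---|
| Unmatched, 27,000 and 90,000 | 121,320 | 726-2,995 | 39-93% |
| Matched 1:3, 27,000 and 81,000 | 112,320 | 672-2,773 | 38-92% |
| Matched 1:1, 27,000 and 27,000 | 58,320 | 349-1,440 | 28-80% |

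**5. The same check at 5% cumulative risk** (the protocol's mortality figure). Unmatched: 121,320 × 0.05 = 6,066 events, power 99.8%. Matched 1:1: 58,320 × 0.05 = 2,916 events, power 98%.

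**The case against.** The strongest reply is that the protocol gives no MI rate for 7% to contradict. The 5% over 4 years is mortality assumed for the surgery comparison, and the trial's 10.0% cannot be turned into an annual rate without a duration. That stands. The conflict is direct for all-cause death, if the surgery figure carries over to drug users, and an inference for MI, though a strong one.

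A reader might go on to infer that the study is underpowered. The documents do not support that. A hazard ratio of 1.16 needs far fewer events than the 1.10 used for sizing (about 2,690 against 6,520 in the available cohort), follow-up beyond one year adds events, and at 5% cumulative risk power is ample. The low figures above come only from an MI rate and follow-up assumed here.

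A reader might also infer that matching by itself undoes the calculation. It need not. No ratio is fixed, 1:3 matching is numerically possible and costs almost nothing, and the cohort exceeds the stated requirement by 42% for sibutramine (27/19) and 55% for orlistat (90/58). Losses from non-overlap remain unknown.

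Finally, the cohort is already extracted, the plan begins with descriptive event rates, and the confidence intervals will show the precision achieved. This limits the harm but does not support the sentence as written. Item 9 itself reports that the trial's excess was confined to patients with pre-existing cardiovascular disease, so an overall hazard ratio of 1.16 may not carry over to this cohort either.

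**Conclusion.** The concern holds in limited form. The sample size follows from its inputs, so this is not an arithmetic error. The fault is that a 7% annual rate with no source and no named event, about 5.5 times the protocol's own annual mortality assumption, is used to conclude that power for MI is adequate. About 2,690 events unmatched, or 1,910 matched 1:1, would have to be expected, and nothing in the protocol shows this.

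Power for a hazard ratio of 1.16 on MI is undetermined: 28-93% across the assumed rates, follow-up and matching ratios, and ample if cumulative risk were near 5%. These ranges rest on proportional hazards, complete use of the 27,000 sibutramine patients, and MI rates and follow-up that are assumptions rather than protocol figures. For all-cause death, power for an effect of that size would be high if the 5% over 4 years applies to drug users.

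**What to change.** In the analysis plan of Amendment item 9:

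1. Replace the 7% with the pooled MI rate, pooled death rate and follow-up observed in the extracted cohort, obtained without comparing the two drugs.
2. State the planned matching ratio and the number expected to remain after dropping non-overlap.
3. From these, give expected events and the detectable hazard ratio for MI, all-cause death and MI in the high-risk subset.
4. Restate the sentence on adequate power to agree with the result, or remove it.

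The cost is one rewritten paragraph and a descriptive tabulation. The stated power may become less favourable. No extra patients and no design change are needed.
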